## Abstract

**Background:**

Total Mesorectal Excision (TME) is the standard surgical technique for the treatment of rectal cancer. However, rates of sexual dysfunction ofup to 50% have been described after TME, and rates of urinary dysfunction of up to 30%. Although other factors are involved, the main cause of postoperative genitourinary dysfunction is intraoperative injury to the pelvic autonomic nerves. The risk is particularly high in the inferior mesenteric artery (IMA). The aim of this study is to compare pre- and post-TME sexual dysfunction, depending on the surgical approach usedin the inferior mesenteric vessels: either directly on the IMA, or from the inferior mesenteric vein (IMV) to the IMA.

**Methods:**

Prospective, randomized,controlled study of patients with rectal adenocarcinoma with neoadjuvant chemoradiotherapy, who will be randomly assigned to one of two groups depending on the surgical approach to the inferior mesenteric vessels. The main variable is pre- and postoperative sexual dysfunction; secondary variables are visualization and preservation of the pelvic autonomic nerves, pre- and postoperative urinary dysfunction, and pre- and postoperative quality of life. The sample will comprise 90 patients, 45 per group.

**Discussion:**

The aim is to demonstrate that the dissection route from the IMV towards the IMA favors the preservation of the pelvic autonomic nerves and thus reducesrates of sexual dysfunction post-surgery.

**Trial registration:**

Ethical and Clinical Research Committee, Parc Taulí University Hospital: ID 017/315. ClinicalTrials.gov TAU-RECTALNERV-PRESERV-2018 (TRN: NCT03520088) (Date of registration 04/03/2018).

## Background

Despite the advances in adjuvant and neoadjuvant chemotherapy (QT) and radiotherapy (RT) for colorectal cancer, surgery remains the only curative treatment [1]. Since its first description by Heald in 1982 [2, 3], Total Mesorectal Excision (TME) has been the standard surgical technique for the treatment of rectal cancer, and has brought about significant improvement in oncological results in terms of both survival and local recurrence [4].

However, the literature describes post-TME rates of urinary dysfunction (urinary incontinence, difficulty in voiding or neurogenic bladder) of up to 30% [5, 6]. The prevalence of sexual dysfunction is above 50%; in men, it includeserectile dysfunction and ejaculation problems, and in women, decreased vaginal lubrication, dyspareunia and difficulty reaching orgasm [5, 6]. For this reason, the study of functional results such as genitourinary function, fecal continence and quality of life in general is taking on increasing importance [1].

Although other factors may be responsible for postoperative genitourinary dysfunction, the main cause is intraoperative injury to the pelvic autonomic nerves [1, 6]. This inadvertent lesion usually occurs due to a lack of anatomical knowledge or due to poor visualization of the nerves [6]. Minimally invasive techniques such as laparoscopic colorectal surgery and robotic surgery have improved surgical technique and surgical visibility, that helps in recognizing the inferior hypogastric plexus [7]. Moreover, a thorough acquaintance with anatomical reference points and experience ofthe dissection during TME reduces the risk of injuring the autonomic nerves, and leaves the mesorectal fascia intact. Indeed, proficient TME technique helps to preserve the autonomic nerves, lowering the incidence of urinary dysfunction from 10 to 30% to 0–12% and sexual dysfunction from 40 to 60% to 10–35% [5, 6]. Table 1 shows the genitourinary dysfunction after TME surgery, with the preservation of the pelvic autonomic nerves [8–10].

**Table 1 Tab1:** Genitourinary dysfunction after TME surgery with preservation of the pelvic autonomic nerves

Author (year)	Surgical approach	N	Measurement methods	Time of measurement	Urinary dysfunction (%)	Sexual dysfunction (%)
Dulskas A, et al. [1] (2016)	Open	108	Urinary: IPSS, BFLUTS Sexual: IIEF, FSFI	Pre-IQ and 6 m postIQ	Men 8.3% Women 11.1%	Men 27.8% Women 11.1%
Pontallier A, et al. [7] (2016)	Lap	34	Urinary: IPSS Sexual: IIEF, FSFI	12 months after closure of the stoma	23.5%	61%
	Transanal	38			31.5%	29%
Liu Z, et al. [8] (2016)	Lap	518	Own scale	At discharge and 6 months postIQ	NE	Ejaculation 42.5% Erection 41.9%
Adam JP, et al. [9] (2016)	Lap	169	Urinary: IPSS Sexual: IIEF, FSFI	Pre-treatment, post-QTRT and 3,6 and 12 months postIQ	17%	Men: Erection 43% Ejaculation 68% Women: Lubrication 62% Dyspareunia 42% Orgasm 57%

*TME* total mesorectal excision, *SP* surgical procedure, *IPSS* International Prostatic Symptom Score, *BFLUTS* Bristol Female Lower Urinary Tract Symptoms, *IIEF* International Index of Erectile Function, *FSFI* Female Sexual Function Index. QTRT: chemoradiotherapy

In rectal cancer surgery particular attention must be paid to certain areas, due to the risk of autonomic nerve damage [6]. Figure 1 depicts the surgical anatomy of the pelvic region and the key points where the risk of injury increases during surgery (Table 2) [5, 6, 11–14]. As described in the table, one of the regions with the highest risk of injury is the inferior mesenteric artery (IMA).

**Fig. 1 Fig1:**
[figure not shown]
Outline of the pelvic autonomic nerves and their target organs

**Table 2 Tab2:** Areas with risk of lesion in the main autonomic nerves, and their effects

Nerve injured		Area of risk	Urinary dysf.	Sexual dysf.
SHP (sympathetic)		Dissection and ligature of IMA	Stress urinary incontinence	Retrograde ejaculation
Hypogastric nerves		Posterior dissection		Alteration in ejaculation (no alteration erection)
Splanchnic nerves (parasympathetic)		Rare in TME In radical lymph node dissections	Neurogenic bladder	Men: alteration erection Women: Dyspareunia
IHP (mixed)		Lateral dissection	Incontinence Difficulty voiding	Problems with ejaculation and erection
- IHP one-sided			Difficulty voiding	Men: Ejaculation and erection problems Women: Problems with genital lubrication
- IHP two-sided			Bladder denervation	Men: impotence Women: dyspareunia and ↓ability to reach orgasm
Neurovascular bundle of Walsh and cavernous nerve		Anterior dissection		Men: impotencia and erectile dysfunction Women:dispareunia and reduced genital lubrication
Pudendo nerve and levator ani		Perineal stage of Miles APR	Urinary incontinence	Sexual sensorial impotence

Recently, Melani [15] described a new laparoscopic approach for the release of the splenic flexure, in which a dissection of the mesenteric vessels is performed from the inferior mesenteric vein (IMV) to the IMA. This route presents a dissection plane that follows the anatomical peritoneal sheets of the retroperitoneum and improves the visualization of the pelvic autonomic nerves from their origin. Compared with the standard approach to the inferior mesenteric vessels (i.e., directly on the IMA), we believe thatthe approach from the IMV to the IMA will improve nerve preservation and thus reduce the incidence of sexual and urinary dysfunction.

## Hypothesis and objectives

### Hypothesis

The hypothesis is that the dissection route from the IMV to the IMA favors the preservation of the pelvic autonomic nerves, and thus reduces genitourinary dysfunction in patients after laparoscopic TME.

### Objectives

The main objective is to determine the pre- and post-TME rates of sexual dysfunction in patients with rectal cancer randomly assigned to one of two nerve preservation techniques.

In both groups, the secondary objectives are to assess: urinary dysfunction pre- and post-TME; the visualization and preservation of the superior hypogastric plexus (SHP), the hypogastric nerves, the inferior hypogastric plexus (IHP) and the Bundle of Walsh; and the impact of genitourinary dysfunction on patients’ quality of life.

## Methods/design

### Study design

In this prospective, controlled randomized study of patients undergoing laparoscopic TME for rectal cancer, with neoadjuvant chemoradiotherapy, patients will be assigned to one of two groups, in a 1:1 ratio: the intervention arm (dissection route from the IMV to the IMA), and the control arm (dissection route directly to the IMA).

### Study area and participants

The study will be carried out at the ParcTaulí University Hospital of Sabadell (Sabadell, Barcelona, Spain), which has a specialized unit for Colorectal Surgery, Urology, Radiodiagnosis, Oncology, and Radiotherapy.

The study population will comprise patients diagnosed with rectal cancerundergoing total colonoscopy with multifocal biopsy, rectoscopy with endorectal ultrasound (ERUS), pelvic magnetic resonance imaging (MRI) and thoraco-abdominal computed tomography (CT). All patients will be evaluated by the multi-disciplinary committee of colorectal tumors and must comply with the following criteria:

### Inclusion criteria

Male sex; age 18 years or over; diagnosis of rectal adenocarcinoma ≤10 cm from the anal verge, measured by rigid rectoscopy, candidate to TME; candidate for neoadjuvant treatment (chemoradiotherapy); scheduled laparoscopic radical TME surgery carried out by colorectal surgeons; ASA I, II or III; provision of signed informed consent.

### Exclusion criteria

Female sex; age under 18; not candidate for neoadjuvant treatment and/or adenocarcinoma > 10 cm from the anal verge candidate to partial TME; abdominoperineal resection (APR); emergency surgery; recurrent tumor; cT4; history of infra-abdominal or pelvic prostate procedures; radiotherapy prior to the current process; patients with severe sexual or urinary dysfunction before surgery; no provision of signed informed consent.

### Criteria for withdrawal

Patients who do not attend the subsequent follow-up.

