### Follow-up

The patient will be referred again to the urologist to repeat the genitourinary dysfunction study 12 months after surgery: Doppler ultrasound of the penis, baseline flowmetry, EHS and the IIEF-5, I- PSS, ICIQ-SF and EORTC-QLQ C30 questionnaires.

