### Study variables

#### Main variable

Preoperative, post-neoadjuvant and postoperative sexual dysfunction at 12 months in all intervened patients will be determined by the urologist, based on the results of the IIEF-5 questionnaire and/or Doppler ultrasound (peak systolic velocity, tele-diastolic velocity and response to vasodilator agent). Scores of 21 or below on the IIEF-5 questionnaire will be taken to indicate sexual dysfunction. The ultrasound will confirm or rule out the presence of sexual dysfunction generated by the test: an adequate response to thevasodilator agent, with blood flow above 35 cm/s in a patient with an altered IIEF-5 or EHS test will be considered a diagnostic criterion for ED of a neurogenic cause.

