#### Analysis of patients by intention to treat, per protocol, and patients lost

Patients will be analysed by intention to treat (ITT), per protocol, andlost patients.

The intention to treat analysis will be applied to all randomized patients.

The per protocol analysis will include part of the group in which direct dissection of the IMA is performed, and all the group that undergo dissection from the IMV to the IMA. Statistical analysis of the lost patients will be performed.

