#### Statistical analysis

To evaluate the main objective of the study, the reduction in sexual dysfunction achieved by the preservation of the pelvic autonomic nerves, we will use the method based on the one-sided confidence interval at 95% of the difference in sexual dysfunction between the two groups [34, 35], in both the intention to treat and per protocol samples.

The quantitative variables will be described giving values of mean and standard deviation, or medians, interquartile interval and range, as appropriate. The categorical variables will be described in absolute numbers and percentages.

The statistical analysis of the quantitative variables, with independent groups, will be performed with the parametric Student’s T-test, provided that its conditions of application are met; otherwise, the non-parametric Mann-Whitney U test will be used.

In the statistical analysis for categorical variables, the Pearson Χ^2^ test or the Fisher exact test will be used.

These methods will be used to compare the baseline characteristicsof the two groups in order to assess whether the randomization has been effective.

Statistical significance will be set at a *p* value of less than 0.05.

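### Withdrawing men who miss follow-up works against the promised intention-to-treat analysis and is likely to leave a comparison of attenders only

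*Protocol article*

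**What the plan says.** The section Criteria for withdrawal consists of a single item: "Patients who do not attend the subsequent follow-up".

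Follow-up schedules one postoperative functional assessment, in which the urologist will "repeat the genitourinary dysfunction study 12 months after surgery". Main variable says that "postoperative sexual dysfunction at 12 months in all intervened patients will be determined by the urologist", using the IIEF-5 and/or penile Doppler, with an IIEF-5 score of 21 or below taken as dysfunction.

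The section on analysis populations names three analyses: "Patients will be analysed by intention to treat (ITT), per protocol, andlost patients". It then states "The intention to treat analysis will be applied to all randomized patients" and, separately, "Statistical analysis of the lost patients will be performed". Under Statistical analysis, the main comparison is a one-sided 95% confidence interval for the difference in sexual dysfunction, to be reported "in both the intention to treat and per protocol samples".

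Sample size asks for 41 patients (read here as per group) and allows for 10% loss to follow-up, giving 45 per group and 90 in total.

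**The concern.** A man who misses the 12-month visit meets the withdrawal criterion and has no postoperative value of the main variable. He nevertheless belongs to the set of all randomized patients. The article does not say how both can hold in an analysis that compares outcomes. Two features suggest how the conflict would be settled in practice: lost patients are listed beside the intention-to-treat and per-protocol analyses, and the sample size is inflated as though lost men add nothing to the comparison. The easy course is to analyse those who attended and call that intention to treat.

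This matters if attendance depends on sexual function. The visit repeats a Doppler study that, as described for the preoperative assessment, involves an injection into the corpus cavernosum, so such a link is plausible, though the article gives no evidence of one. Loss that depends on outcome, and does so differently by arm, biases the main comparison. Withdrawal also ends the chance of obtaining the outcome another way, and a later analysis plan cannot repair that.

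**Working it through.** **Inputs.** From Sample size: 50% v 20% dysfunction, one-sided 5% level, 90% power, 41 evaluable and 45 recruited per group, 10% loss. Assumed here: 4 lost per arm (45 − 41), and the outcomes of the lost men.

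**The plan's own figure.** The usual normal-approximation formula for two proportions (pooled variance under the null, no continuity correction) gives 42 per group; the arcsine version gives 41.4 before rounding. The stated 41 is reproduced to within one patient, with power 89.7%. For loss, 41 × 1.1 = 45.1, close to the stated 45 (41/0.9 would give 46).

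**Power.** It is 92.1% with all 45 per group analysed and 89.4% with 10% missing (40.5 per group). Loss of power is not the issue.

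**Shift in the estimate.** Let x and y be the dysfunction rates among the 4 lost men in the control and intervention arms. The all-randomized difference is

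[41 × (0.50 − 0.20) + 4 × (x − y)] / 45 = 27.3 + 8.9 × (x − y) points.

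| Assumption about lost men | Difference, points |
|---|---|
| Attenders only | 30.0 |
| Same rate in both arms (x = y) | 27.3 |
| No lost control, every lost intervention man has dysfunction | 18.4 |
| Every lost control, no lost intervention man has dysfunction | 36.2 |

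The standard error among attenders is √[(0.25 + 0.16)/41] = 0.100, or 10 points. Equal rates move the estimate by 2.7 points, 0.27 of a standard error. The unfavourable extreme moves it by 11.6 points, a little over one standard error.

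**Effect on the conclusion.** In whole patients, the lower bound is d − 1.645 × √[p₁(1−p₁)/n₁ + p₂(1−p₂)/n₂].

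| Case | Control v intervention | Difference, points | Lower bound, points |
|---|---|---|---|
| Planned effect, attenders | 20/41 v 8/41 | 29.3 | +12.9 |
| Planned effect, worst case | 20/45 v 12/45 | 17.8 | +1.5 |
| Borderline, attenders | 20/41 v 12/41 | 19.5 | +2.1 |
| Borderline, 2 lost men with dysfunction in each arm | 22/45 v 14/45 | 17.8 | +1.1 |
| Borderline, 1 such man in the intervention arm only | 20/45 v 13/45 | 15.6 | −0.9 |
| Borderline, worst case | 20/45 v 16/45 | 8.9 | −8.0 |

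The planned effect survives even the worst case. The borderline result survives equal outcomes among the lost men, but a difference of one man between the arms is enough to reverse it.

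**The case against.** The strongest reply is that the article says in words that intention to treat covers all randomized patients and never removes lost men from that set. The lost-patient analysis may be no more than a description of attrition, and the 10% allowance is a planning margin that defines no population. All of this stands. A reader might infer that the article defines its intention-to-treat set as attenders only; the text does not support that. It supports only the statement that the rules conflict and that this outcome is likely.

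A reader might also take "in all intervened patients" as a second, narrower analysis set. It describes who is measured. Assignment is placed directly before surgery, so randomized and operated men should nearly coincide. It adds nothing to the case.

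How to impute a missing outcome can properly sit in an analysis plan that is not shown, and its absence here is no finding. The withdrawal rule is different, because it is stated here and governs what data will exist.

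Finally, the size is easily overstated. Patient and urologist are blinded, which makes loss driven by knowledge of the arm less likely, and dysfunction-related absence shifts the difference appreciably only if the lost men's outcomes differ by arm. The 18.4 to 36.2 range needs opposite extremes in the two arms. Blinding does not, however, stop absence driven by function itself, which the trial expects to differ between arms.

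**Conclusion.** The concern holds in a limited form. The withdrawal rule, the single 12-month outcome and the separate lost-patient analysis conflict with intention to treat on all randomized patients. Followed as written, they are likely to yield an attenders-only comparison under that name.

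At the planned loss the effect on the estimate is modest under equal outcomes among lost men (30 to 27.3 points) and substantial only under opposite extremes. The planned 30-point effect would not be overturned; a result close to the significance boundary could be. The rates, sample size and 10% loss are the article's own. The 4 lost per arm, their outcomes and the borderline counts are assumptions used to show a range, not forecasts. The point should be corrected, but it does not invalidate the design.

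**What to change.** 1. Reword Criteria for withdrawal so that only withdrawal of consent ends participation and a missed visit is recorded as a missing outcome.
2. In the section on analysis populations, state that non-attenders remain in the intention-to-treat set, and that the lost-patient analysis is descriptive only.
3. Offer the five-question IIEF-5 by post or telephone, through staff unaware of the arm, to men who do not attend. This fits the existing definition, which allows IIEF-5 and/or Doppler and already sets the cut-off at 21.
4. For outcomes still missing, report a best/worst-case sensitivity analysis: all missing men counted as having dysfunction in one arm and none in the other, then the reverse.

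The choice of imputation model can be left to the analysis plan.

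The cost is a change of wording, a handful of questionnaires (about 4 or 5 men per arm at 10% loss) and a little more analysis. The drawback is that a few outcomes would rest on the questionnaire without the Doppler result that the article uses to confirm or rule out dysfunction; their number should be reported by arm.

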### Definitions

Sexual dysfunction (SD) is defined as difficulty at any stage of sexual intercourse (which includes desire, arousal, orgasm and resolution) that prevents the individual or their partner from enjoyingsexual activity [16]. Erectile dysfunction (ED) is defined as the persistent inability to reach and maintain an erection sufficient to allow satisfactory sexual performance, which mayhave a physical and psychological effect on health and have a significant impact on the quality of life of patients and their respective partners [17].

According to the *2017 European* Association of *Urology* (EAU) *guidelines*, the diagnostic evaluation should be carried out with a correct anamnesis, the use ofvalidated questionnaires such as the International Index of Erectile Function or IIEF-5[18] and the Erection Hardness Score (EHS) [19], a full physical examination and basic analytical parameters such as total testosterone levels [17]. In addition, Doppler ultrasound of the penis is recommended, with the aim of recording objective parameters of induced erection so as to identify the cause of ED [17].

The IIEF-5 questionnaire consists of five questions that are scored from 0 to 5. Scores of 21 or lower are considered to indicateED. The test also classifies the severity of the ED as mild (score 17–21), mild to moderate (score 12–16), moderate 8–11 or severe (score 1–7) [18].

The EHS classifies erections in four grades: grade 1 or severe (does not allow penetration); grade 2 or moderate (increased circumference, relatively rigid, but not enough to achieve penetration); grade 3 or mild (increased length and circumference to allow penetration, but not enough to be satisfactory); grade 4 (maximum dimensions in terms of length and strength to achieve satisfactory penetration) [19].

Urinary or voiding dysfunction is defined as any alteration in the correct functioning in the storage or periodic emptying of urine, either in isolation or simultaneously [20]. To measure the severity of symptoms and the impact on the quality of life, or to monitor the response to a particular treatment, the ICIQ-SF (International Consultation on Incontinence Questionnaire) is used [21]. The ICIQ-SF consists of three questions, with a total score of 1 to 21; a score higher than 0 is considered a diagnosis of urinary incontinence.

The IPSS (International Prostate Syndrome Score) [22] consists of seven questions that assess voiding, frequency, intermittency, urgency, weak stream and effort. Each question is scored from 0 to 5: an overall score of 1 to 7 reflects mild symptomatology, one from 8 to 19 moderate, and from 20 to 35 severe. However, the only method that can objectively evaluate the filling and emptying phase, and therefore diagnose the presence and type of urinary dysfunction, is the urodynamic study [20].

### Informed consent and legal considerations

Patients will be informed, both orally and in writing, of the objective and duration of the study. It will be made clear that participation is voluntary and they will be informed of all the possible risks and associated complications. Patients who meet the inclusion criteria and sign informed consent will enter the randomization process. They may withdraw their consent to participate at any time.

The variables described are recorded in a computerized database (Microsoft® Acces 2003). The data will be introduced in a protected format to avoid (as far as possible) the entry of out-of-range or anomalous values. The patients’ data will berecorded anonymously and in accordance with the Spanish legislation on data protection (LOPD, 1999) [23].

The study protocol, the patients’data and the informed consent documents have been approved by the Clinical Research Ethics Committee in accordance with the 2015 Royal Decree on medical trials with drugs. The Parc Taulí’s ethics committee will serve as the reference (ID: 2017/315). The study has been registered in the ClinicalTrials.gov database (ID: NCT03520088).

The trial will be carried out in accordance with the 7th Revision of the Declaration of Helsinki [24] and follows the guidelines of the 2013 SPIRIT Standard Protocols for Clinical Trials [25],CONSORT 2010 for Clinical Trials [26],and the Spanish Agency for Medicines and Health Medical Products).

